## Methods

### Recruitment process

Patients with MPE from any primary tumour visible with bedside ultrasound and drained at least one time are eligible for inclusion (Table 1). Patients with MPE who are eligible for PITAC are identified during the multidisciplinary tumour (MDT) conference. Bilateral MPE is acceptable, but the most affected side at the time of inclusion will be treated throughout this study. In case of symptomatic MPE on the contralateral side, the patient may be included as a new patient after the last follow-up.

**Table 1: j_pp-2024-0014_tab_001:** Inclusion and exclusion criteria.

Inclusion criteria	Exclusion criteria
– Symptomatic MPE visible with bedside ultrasound – Histologically or cytologically verified malignancy (primary tumour) – Status CT-scan not older than four weeks – MPE requiring at least one drainage procedure – Drained ≥14 days before the first PITAC directed treatment – Bidirectional systemic chemotherapy or immunotherapy ≥14 days before the first PITAC directed treatment or no simultaneous systemic chemotherapy or immunotherapy – ECOG performance status 0-2 – Life expectancy ≥3 months – Age ≥18 years – Fertile women must have a negative pregnancy test at time of inclusion and use adequate contraception – Danish-speaking and reading patients	– A history of allergic reaction to cisplatin or other platinum containing compounds or doxorubicin – Renal impairment, defined as GFR<40 mL/min (cockcroft-gault equation) – Myocardial insufficiency, defined as NYHA class>2 – Impaired liver function defined as bilirubin≥1.5*xULN* – Impaired bone marrow function defined as platelets≤100*x*10^9^/L – Any other condition or therapy, which in the investigator´s opinion may pose a risk to the patient or interfere with the study objects

CT, computed tomography; ECOG, eastern cooperative oncology group; GFR, glomerular filtration rate; MPE, malignant pleural effusion; NYHA, New York heart association; PITAC, pressurized intrathoracic aerosol chemotherapy; PLM, pleural metastasis; ULN, upper limit of normal.

All personnel will be informed about the procedure both orally and in writing, including occupational health aspects. Only those who volunteer will take part in the PITAC procedure.

Patients will be excluded from the study if (1) requested by the patient, (2) access to the pleural cavity is not possible due to adhesions or other technical aspects, and/or (3) decline in general health resulting in Eastern Cooperative Oncology Group (ECOG) performance status higher than 2. Following events are considered sufficient reasons for discontinuing a subject from the study (1) withdrawal of consent, (2) death, (3) loss to follow up and/or (4) severe AE or surgical complications. The following information will be recorded for patients who have been excluded from the study: Survival, amount and frequency of MPE drainages and illness specific variables (e.g. CT-scan results).

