### Pressurized IntraThoracic Aerosol Chemotherapy (PITAC)

The first treatment with PITAC for MPE was performed in Germany in 2012. The concept of PITAC is based on experience from Pressurized IntraPeritoneal Aerosol Chemotherapy (PIPAC) [3]. PIPAC is feasible and safe in the treatment of peritoneal metastasis (PM) 12], [13], [14. In addition, PIPAC directed therapy is repeatable with 4–6 week intervals, and the patients may be discharged at postoperative day 0–1 without significant toxicity [13]. The intraperitoneal nebulization of chemotherapy under high pressure increases distribution and penetration of cytotoxic agents to the peritoneum, which may decrease fluid production 15], [16], [17. Theoretically, it should be possible to achieve the same effects in the intrapleural space when using PITAC, but whether this is feasible, safe and able to provide local response is uncertain [18].

To date, data on 21 patients treated with 38 PITACs have been published worldwide, and at Odense PIPAC Center (OPC), five patients have been treated with 11 PITAC procedures (two non-access). The primary indications were MPE and/or pleural metastasis (PLM) due to malignant mesothelioma, gastric cancer, ovarian cancer, rectal cancer, or breast cancer. A recent review by Hansen et al. suggests that PITAC is feasible, but more prospective data are needed to evaluate patient and personnel safety, and potential local effect [3, 15, 19], [20], [21], [22.

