#### Primary and secondary objectives

This is a Phase-I study investigating safety and feasibility of repeated PITAC (minimum of two procedures) in 20 patients. PITAC is considered feasible and safe if four patients or less have severe surgical complications defined as Clavien-Dindo ≥ 3b or life-threatening adverse events (AE) defined as Common Terminology Criteria for Adverse Events v. 6.0 (CTCAE) ≥ 4 within 30 days after the procedure. All medical AEs and surgical complications will be recorded, but only those who are probably or certainly/definitely related to the PITAC directed treatment will provide grounds for assessing the feasibility and safety.

Secondary objectives include (1) macroscopic evaluation of PLM before and after PITAC and evaluation of histological response using a proposed Thoracic Regression Grading Score (TRGS) in biopsies from visible PLM and MPE [23], (2) evaluation of response by pleural lavage fluid (PLF) or MPE cytology, (3) assessment of personnel safety (environmental and biological), and (4) evaluation of the quality of life with EORTC-QLQ-C30 at baseline, day 30 and three months after the last PITAC directed treatment.

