### Sample size

There are no data to support the estimated number of patients needed for this phase-I study. The non-access rate, based on previous experience, is estimated to 20 %. This study will include consecutive MPE patients until 20 patients have completed at least two PITAC procedures. Interim analyses will be performed in order to monitor patient safety.

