#### Interim analysis

The reported risk of serious complications during standard thoracoscopy is approximately 5 % [30, 31]. Based on our preliminary experience with PITAC and the limited data from the literature, the risk of adding PITAC to a standard thoracoscopy seems low. However, since the actual risk of PITAC is unknown, we choose to perform an interim safety analysis after every 10 procedures. The study will be discontinued if four or more procedures have led to patients having Clavien-Dindo ≥ 3b or CTCAE≥4 complications/adverse events.

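### The 'feasible' verdict rests on severe complications alone, while patients who cannot be accessed or who stop early are in effect replaced, so access and completion rates cannot alter it

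*Protocol article*

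**What the plan says.** **Question and verdict.** Under Primary and secondary objectives, the protocol article describes a phase-I study of the safety and feasibility of repeated PITAC, with at least two procedures per patient. One rule serves both: "PITAC is considered feasible and safe if four patients or less have severe surgical complications" (Clavien-Dindo 3b or higher) or adverse events of CTCAE grade 4 or higher within 30 days. Only events judged probably or definitely related to treatment "will provide grounds for assessing the feasibility and safety".

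**Non-access.** Under Recruitment process, a patient is excluded if "access to the pleural cavity is not possible due to adhesions or other technical aspects". The rule is not limited to the first attempt. Some data are kept: "The following information will be recorded for patients who have been excluded from the study: Survival, amount and frequency of MPE drainages", together with illness-specific variables such as CT results.

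**Recruitment.** The Sample size section states: "This study will include consecutive MPE patients until 20 patients have completed at least two PITAC procedures". It also states: "The non-access rate, based on previous experience, is estimated to 20" %. No maximum number of patients and no limit for non-access is given. The introductory section on PITAC gives the centre's own experience: "five patients have been treated with 11 PITAC procedures (two non-access").

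**Elsewhere.** Neither the access rate nor the two-procedure completion rate is among the primary or secondary objectives. The interim rule also counts only severe events.

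**The concern.** For a procedure that must be repeated, feasibility depends on whether the pleural space can be entered and whether patients reach the second procedure. The plan expects a material failure rate on the first of these, yet neither quantity enters its verdict. The 20 patients in the target sample are defined by having succeeded on both.

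The same applies to patients who stop after one PITAC because of death, decline in performance status, withdrawal or a severe event. They are not among the 20 completers, and the article does not say whether their events count towards the limit of four patients.

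At stake is a published conclusion that PITAC is feasible, which would not describe the patients in whom it was attempted. The abstract says the results may significantly affect the next steps in implementing PITAC, so the conclusion would carry weight.

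**Working it through.** **Inputs**
- Verdict: positive if at most 4 patients have a related severe event (Primary and secondary objectives).
- Target: 20 patients with at least two PITACs (Sample size).
- Expected non-access: 20% (Sample size).
- Pilot: 2 non-access, 11 procedures, five patients (introductory section on PITAC).
- Background risk: "The reported risk of serious complications during standard thoracoscopy is approximately 5" % (Interim analysis).
- Assumptions: independence as stated below; 50% and 60% non-access are illustrations, not plan figures.

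**1. The plan's own figures.** The 20 completers come without an error rate, power or target rate, so there is no calculation to reproduce. The 20% is close to the pilot: 2/11 = 18.2%. If the two failures were additional to the 11 procedures, it is 2/13 = 15.4%.

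**2. How well the 20% is known.** The exact (Clopper-Pearson) 95% interval for 2/11 is 2.3% to 51.8%. This treats 11 procedures in five patients as independent, which is doubtful because adhesions may recur in the same patient.

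**3. Starters needed for 20 completers,** counting non-access as the only loss. With non-access rate q, the number is 20/(1 − q) if q applies once per patient, and 20/(1 − q)² if it applies independently to each of two procedures.

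| q | once per patient | per procedure, independent |
|---|---|---|
| 20% | 20/0.8 = 25 | 20/0.64 = 31.25 |
| 50% | 20/0.5 = 40 | 20/0.25 = 80 |

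Under the second reading, 0.8 × 0.8 = 64% of starters complete two procedures at q = 20%, and 0.5 × 0.5 = 25% at q = 50%.

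**4. Chance of a positive verdict.** With X ~ Binomial(20, p), where p is the severe-event risk per patient and events are counted in the 20 completers:

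| p | P(X ≤ 4) |
|---|---|
| 5% | 99.7% |
| 10% | 95.7% |
| 15% | 83.0% |
| 20% | 63.0% |
| 30% | 23.8% |

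The rate q appears nowhere in this calculation, so each value holds at any q at which 20 completers can be found. For example, with 60% non-access once per patient, 20/0.4 = 50 starters are needed and 30 of the 50 fail access (exact 95% interval 45% to 74%). At p = 5% the verdict is still positive with probability 99.7%.

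**5. If events in all starters counted.** The article leaves this open. Suppose all 50 starters carried the same 5% risk. Then P(X ≤ 4) with X ~ Binomial(50, 0.05) is 89.6%. Non-access would now lower the chance somewhat, but only because more patients contribute events. The access failure itself would still not count.

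**The case against.** **The rule can fail.** A reader might infer that the trial can never return a negative answer on feasibility. That is not so: five or more patients with related severe events give a negative verdict, and at a 30% event risk the positive verdict has only a 23.8% chance. What stands is narrower: access and completion do not influence the verdict.

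**Excluded patients are not lost altogether.** Survival, drainage amount and frequency, and CT results are still recorded. The 30-day follow-up must be collected before the next PITAC, so complications of a first procedure should be known before a second attempt fails. Biopsies, the macroscopic score and intraoperative fluid samples need access, and no analysis rule can supply them at a failed attempt. This stands, although quality of life is not named in the list of data kept. A patient who fails access only at the third procedure has already completed two and counts among the 20.

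**Non-access is not ranked.** The documents give it an expected rate and list it as one reason for exclusion. They do not call it the main technical failure.

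**Safety is the stated aim.** The Aim section speaks of patient and personnel safety, and consecutive inclusion allows attempts and failures to be reported descriptively. An unseen full protocol or analysis plan may tabulate them. That is fair, but the article itself fixes the rule for calling PITAC feasible and limits what may inform it, so a descriptive table would not change the verdict.

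**Conclusion.** The point holds as a fault in how 'feasible' is defined. If the severe-event limit is met and 20 completers can be recruited, the verdict is the same at any access or completion rate. That replacement takes place is inferred from recruiting until 20 patients have completed; the article does not use the word.

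The verdict could then rest on 20 of 25 to about 31 starters at the plan's own 20%, and on 20 of 40 to 80 at an illustrative 50%. The upper figure in each range assumes independence between procedures; the lower takes the rate as per patient. The pilot interval of about 2% to 52% does not rule out a poor access rate. The safety reading of the complication count is not at issue here. The correction should be made before a claim of feasibility is published.

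**What to change.** 1. Use the count of related severe events for the safety verdict only, and state whether events in patients with fewer than two procedures count towards it.
2. Judge feasibility on (a) the access rate per attempted procedure and (b) the share of all patients with a first access attempt who receive two PITACs, each with an exact 95% interval. For (a), note that attempts cluster within patients.
3. Tabulate reasons for not completing two procedures, with technical non-access kept apart from death, decline or withdrawal. In a population with a life expectancy of 3 to 12 months, (b) alone would mix these.
4. Read (a) against the expected 20% non-access as a planning benchmark, or prespecify an explicit limit. The 20% should not become a pass mark by default: with 25 first attempts, requiring at most 5 failures would be met only 62% of the time at a true rate of 20%. An illustrative limit of 8 in 25 would be met 95% of the time at 20% and 5% at 50%.
5. Keep patients with non-access after a completed PITAC in the safety analysis and in the outcomes obtainable without access: drainage volume, quality of life, CT and survival.
6. If none of this is adopted, restrict the conclusion to safety.

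The cost is mainly protocol wording, because attempts and access failures are known at surgery; quality of life would need to be added to the data kept on excluded patients. The downside is a less favourable feasibility figure.

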## Introduction

When the spread of cancerous cells to the pleural cavity disrupts the equilibrium between absorption and excretion of fluid, the result is malignant pleural effusion (MPE) [1, 2]. Mesothelioma, lymphoma, lung, breast, ovarian, and gastrointestinal cancers are the most frequent causes of MPE [3]. MPE indicates an advanced disease with high mortality, poor quality of life and a life expectancy of 3–12 months [1, 4, 5]. The patients present with progressive shortness of breath, chest pain, cough and weight loss [5]. Recent research has suggested that MPE furthermore promotes tumour growth and chemotherapy resistance [6]. The exact incidence of MPE in Denmark is unknown, but is estimated to approximately 5,000 new cases per year and found equaling 15 % of all cancer patients [5, 7].

The available treatments for symptomatic MPE are suboptimal and with limited influence on patient’s life expectancy as these interventions focus only on relief of symptoms, and 90 % of the patients require repeated interventions [8, 9]. They include intermittent pleural drainage, indwelling pleural catheters, and chemical pleurodesis [5, 10]. Pleurodesis has shown a potential increase in survival suggesting that local treatment of the pleura should be prioritized [11].

Patients with MPE who are in a good general condition and with a remaining life expectancy of more than a few months may have an unmet need for additional treatment, in order to increase their quality of life [9]. Often, these patients have developed loculations, hindering complete drainage of MPE and undergone several different treatments with disappointing results. Hence, new and more effective treatment strategies are needed.

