### Study intervention and procedures

The patients will be scheduled for clinical assessment in the PITAC outpatient clinic including bedside ultrasound of the pleural cavity and information about the study. Included patients will be scheduled for a maximum of three PITAC procedures and minimum of two PITAC procedures at four-week intervals (Figure 1).

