### Postoperative procedure

The patient is monitored for a minimum of one day. A chest X-ray is performed if the patient shows signs of respiratory distress to consider the indication for a chest tube. SAT, FEV1, and reactions/complications will be registered before discharge of the patient.

Thirty days after each PITAC directed therapy the patient will attend an outpatient appointment for bedside ultrasound and registration of postoperative reactions/complications. The 30 day follow-up must be collected prior to the next PITAC directed treatment.

The last follow-up including a CT scheduled three months after the last PITAC. Furthermore, patients will be evaluated in the outpatient clinic including bedside ultrasound, SAT and FEV1.

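### The three-month quality-of-life result comes only from patients who are alive and were not excluded for a fall in performance status, so it is likely to favour PITAC

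*Protocol article*

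**What the plan says.** Under Primary and secondary objectives, the fourth secondary objective is "evaluation of the quality of life with EORTC-QLQ-C30 at baseline, day 30 and three months after the last PITAC directed treatment".

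Under Recruitment process, one ground for exclusion from the study is "decline in general health resulting in Eastern Cooperative Oncology Group (ECOG) performance status higher than 2". The others are the patient's own request and failed access to the pleural cavity. The same paragraph gives a separate list of sufficient reasons for discontinuation: "withdrawal of consent, (2) death, (3) loss to follow up and/or (4) severe AE or surgical complications".

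The paragraph ends with what is kept for excluded patients: "The following information will be recorded for patients who have been excluded from the study: Survival, amount and frequency of MPE drainages", together with illness-specific variables, for which CT results are the example. Quality of life is not named. Nothing is said about what is kept for discontinued patients.

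On timing, Study intervention and procedures plans "a maximum of three PITAC procedures and minimum of two PITAC procedures at four-week intervals", and Postoperative procedure states "The last follow-up including a CT scheduled three months after the last PITAC". Table 1 requires "Life expectancy ≥3 months" at entry, and the Introduction gives "a life expectancy of 3–12 months" for malignant pleural effusion in general.

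**The concern.** The exclusion rule and the outcome respond to the same thing. Worsening general health should show in the QLQ-C30, yet once it takes ECOG above 2 it removes the patient from the study, and the questionnaire is not among the data still collected. The missing values are therefore the poor ones, and the protocol itself creates the gap. A statistical analysis plan can decide how to treat missing questionnaires, but it cannot recover ones that were never collected.

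Death before the visit adds to the selection, because the last questionnaire falls later than the minimum life expectancy required at entry.

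The Introduction presents better quality of life as part of the unmet need in these patients. The study has one arm, so no comparison group would reveal the selection. A stable or improved three-month score among responders could be read as benefit while the treated group as a whole was getting worse.

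**Working it through.** The article states no attrition, power or precision figure for quality of life, so there is no figure of its own to reproduce. The check covers what is collected, when, and from how many patients.

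**1. What is collected.**
- Planned: QLQ-C30 at baseline, day 30 and three months after the last PITAC.
- Kept after exclusion: survival, drainages, illness-specific variables.
- Common to both lists: no quality-of-life item.

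**2. When the last questionnaire falls.** Inputs: two or three procedures at four-week intervals, and a visit three months after the last. One month is 365.25/12 = 30.44 days. For k procedures, time from the first PITAC = 28(k − 1)/30.44 + 3 months.
- k = 2: 28/30.44 + 3 = 3.9 months.
- k = 3: 56/30.44 + 3 = 4.8 months.

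**3. Where day 30 falls.** The objective does not say which PITAC it follows.
- After the first: 30/30.44 = 1.0 month.
- After the last: (28 + 30)/30.44 = 1.9 months, or (56 + 30)/30.44 = 2.8 months.

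Selection is therefore absent at baseline, limited at day 30 if that follows the first PITAC, greater if it follows the last, and strongest at three months.

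**4. How many are alive at the three-month visit.** Sample size recruits until 20 patients have completed at least two PITACs, so each of the 20 is alive at the last procedure received. Assume exponential survival from that point, with the 3 to 12 months in the Introduction read as a range of medians. Then the share alive three months later = 0.5^(3/median).

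| Assumed median (months) | Share alive | Of 20 |
|---|---|---|
| 3 | 0.5^(3/3) = 0.500 | 10.0 |
| 6 | 0.5^(3/6) = 0.707 | 14.1 |
| 12 | 0.5^(3/12) = 0.841 | 16.8 |

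These counts are before any exclusion for ECOG above 2. That exclusion lowers them further, by an amount the article does not give.

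**5. Direction.** Among patients alive at the visit, let p be the share who answer. If responders have mean change R and the others N, the responder mean exceeds the mean of all living patients by (1 − p)(R − N). Patients removed because their general health fell should have the lower change, so R − N is expected to be positive and the error favours PITAC. The article gives no value for p, R or N, so the size of the error cannot be calculated.

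**The case against.** The strongest reply is that this is a 20-patient phase-I safety study, that quality of life is its fourth secondary objective, and that no hypothesis or decision depends on it. The article also condenses a fuller protocol that may keep more data, and it names no quality-of-life mean, analysis population or missing-data rule that could be faulted. Extra questionnaires cannot cure loss through death.

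Much of this stands. It limits the weight of the point and rules out criticism of an analysis the article does not describe. It does not remove the point, because the article gives a specific list of what is kept after exclusion and the QLQ-C30 is not on it. Deaths cannot be measured around, but they can be counted in the denominator.

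The documents do not support several stronger readings that a reader might infer:
- **That quality of life is measured only in patients who reach the last visit.** Baseline and day-30 questionnaires are also planned, and patients who decline later can complete them.
- **That as few as 6 or 7 of the 20 would be alive at that visit.** Running survival from the first PITAC with a median of 3 months gives 20 × 0.5^(4.84/3) = 6.5. However, the 20 are counted as completers of two procedures, so they are already alive at the last one. Even the 3-month median is pessimistic for patients selected on ECOG 0–2 and at least 3 months' expectancy.
- **That failed access shrinks the 20 much further.** Patients without access at the first or second procedure have not completed two and are replaced. Only failed access at a third could matter.
- **That every severe event ends measurement.** Such events are listed as sufficient reasons for discontinuation, which is permissive, and the list of kept data is written for excluded patients.
- **That timing the visit from the last PITAC is an error.** It gives equal time since last treatment. Another anchor is a matter of preference.
- **That the 30-day questionnaire after each PITAC is missing.** A visit 30 days after each procedure is planned, and the flow chart, not shown here, may place the QLQ-C30 there.

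**Conclusion.** The point holds for the three-month QLQ-C30 result. As written, that result comes only from patients who are alive and were not excluded for ECOG above 2, so it is selected toward those who did not decline and is likely to favour PITAC. Baseline is unaffected. Day 30 is less affected, to a degree that depends on which PITAC it follows. The primary safety criterion is not touched by this point.

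The size is illustrative: about 10, 14 or 17 of 20 alive at the visit for medians of 3, 6 or 12 months, and fewer answering once exclusions for decline are taken out. This rests on exponential survival from the last PITAC and on reading a general life-expectancy range as medians; neither is stated in the article. The finding about what is collected needs no such assumption. The change should be made, because data lost this way cannot be recovered later, but the point concerns a secondary objective only.

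**What to change.** In the exclusion and discontinuation paragraph under Recruitment process, add the QLQ-C30 at its planned time points to the data recorded afterwards. Apply this to every patient who received at least one PITAC, whether excluded or discontinued, until death or withdrawal of consent. Collection can be by post or at existing contacts. No treatment or exclusion rule needs to change.

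Report the three-month result with all treated patients in the denominator. Show how many died, how many could not answer, and the share alive and not worse than baseline, beside the mean in responders.

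The cost is a short amendment and a few more questionnaires from ill patients, some of which will still be missing. The quality-of-life result may look less favourable.
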